**Primary objective**

The primary objective of this study is to compare the effect of whole-body electrostimulation and conventional resistance training on functional capacity, muscle strength, walking speed, risk of falling, and lean mass among elderly subjects.

**Secondary objective**

The secondary objectives of this study are to compare the effect of whole-body electrostimulation and conventional resistance training in reducing the fear of falling and increasing the social participation among elderly subjects.

**Procedures and Instruments:**

This will be a randomized, prospective, clinical trial to be conducted in the Laboratory of Movement Analysis of the Federal University of Juiz de Fora School of Physical Therapy. The subjects will be invited for participation by publicizing the study through posters at the university, personal communication, and dissemination through the internet and social networks. Participants will be informed and guided about the evaluations and objectives of the research, and those agreeing to participate will be asked to sign a Free and Informed Consent Terms. The evaluations will be initiated only after participants sign the Informed Consent Term. Participants will be instructed to wear comfortable clothing and appropriate footwear, and will be advised not to perform strenuous exercises at least 24 hours before the assessment and the exercise sessions. The allocation to the experimental and control groups after the baseline evaluation will be at random, using a table of random numbers.

All participants will be subjected to the evaluations described below, at baseline, immediately after the intervention, and eight weeks after the intervention. Questionnaires to evaluate the fear of falling and degree of social participation will also be administered at the same time points. The baseline assessment as well as re-evaluation after eight weeks of intervention will last approximately 40 minutes each. After the first re-evaluation, the subjects will be monitored at intervals of 3 and 6 months through the questionnaires about degree of social participation and fear of falling. These will be done through phone calls and will assess whether the effect of the training has been maintained over a year. The call for answering the questionnaire will last a maximum of 15 minutes, which will be the average response time for both questionnaires (Table 2).

Screening: The Screening Instrument (ANNEX 1) will be used to collect the data about demographic (e.g. age, gender) and clinical characteristics (medications, co-morbidities, clinical history, and family history).

The Six-Item Screener (SIS) (Annex II) is a simple tool to identify cognitive impairment. It was developed by Callahanet al. (2001), derived from the *Mini-Mental State Examination.* It can be administered over the phone or in the form of an interview. Its score ranging between zero and six, is easily marked by a simple sum of errors and consists of parameters to check the temporal orientation (three items) and late memory (three items). SIS will be administered soon after the Screening Instrument and patients who score less than four will be considered as having cognitive impairment and will be excluded from the study.

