**Drawing:**

This will be a randomized, prospective, clinical trial to be conducted in the Laboratory of Movement Analysis of the Federal University of Juiz de Fora School of Physical Therapy. Participants will be informed about the objectives of the research and those who agree to participate will be asked to sign the informed consent form. After approval from the research ethics committee, the trial will be registered in the Brazilian Clinical Trial Registries (REBEC) platform. Elderly subjects over 60 years of age from both sexes, will be eligible for the study. They will be examined in the geriatric ambulatory service of the university hospital of the Federal University of Juiz de Fora (HUCAS/UFJF). The subjects will be invited for participation by publicizing the study through posters or by invitation of the researcher in the waiting room, during their consultation visits to the ambulatory service. The evaluations will be initiated only after participants sign the Informed Consent Term. After checking for the eligibility criteria for inclusion in the study, the participants will be evaluated for the functional tests: walking speed, sit-up test, and the Timed Up and Go (TUG) test. Body composition will also be evaluated by analysis of the lean mass and fat mass using electrical bioimpedance. In addition, muscle strength during knee extension will be tested. Interviews will be conducted through questionnaires to enquire about their social participation and any fear of falling that they might have. After the 8-week intervention period, all parameters will be re-evaluated. The subjects will be followed up at 3 and 6 months, and re-evaluated through questionnaires about their fear of falling and to check their social participation. Participants will be randomly assigned to one of the two arms of the study, namely, electrostimulation group, or resistance training group. The electro-stimulation group will receive training based on whole-body electrostimulation (WB-EMS). Previous references that showed satisfactory results in the elderly with whole-body electrostimulation, will be used to define the electrostimulation parameters (Kemmler et al, 2014, 2013). The electro-stimulation group will be subjected to 18 minutes of electrical muscle stimulation, two sessions per week, for 8 weeks. The regimen will be as follows: an intermittent bipolar electric current with a frequency of 85 Hz, pulse width of 350 μs with 6 seconds of stimulation and 4 seconds of rest. The thigh, arm, abdomen, thorax, cervical and thoracic paravertebral muscles, and large muscles on the dorsal side will be stimulated. The **Resistance training group** will undergo two training sessions per week, with supervised resistance exercises involving the same set of muscles as those in the electro-stimulation group, but without electro-stimulation. They would be subjected to a load of 50 to 80% of one repetition maximum test (1-RM) for a period of 8 weeks. After the first reassessment, the subjects will be followed up at intervals of 3 and 6 months, and will be evaluated through questionnaires to check their social participation and fear of falling.

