**Data analysis methodology:**

**Statistical analysis**

SPSS version 20.0 will be used. The data will be presented as average and SD or median and interquartile. Statistical analysis by intention to treat will be performed using the unpaired t-test or Mann-Whitney test. The effect size will be determined for each variable of interest. Analysis of mixed models, including the outcomes measured at the 4 time points (basal, immediately after intervention, and at 3 and 6 months) will be performed. The "time point" will be included as a class variable. Group, time, and group * time interactions will be inserted. This will evaluate the sole effect of the intervention, since the difference from baseline values at each time point will be evaluated. A value of p = 0.05 will be assumed for all tests.

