**Execution Schedule:**

Data collection will begin only after the project has been approved by the CEP.

| **Stage Identification** | **Start (DD/MM/YYYYY)** | **Termination (DD/MM/YYYYY)** |
| --- | --- | --- |
| Training the team on the study procedures | 01/03/2021 | 01/04/2021 |
| Data Collection | 04/05/2021 | 09/05/2022 |
| Data analysis | 12/05/2022 | 17/10/2022 |
| Screening of participants | 02/04/2021 | 05/10/2021 |
| Writing the final report and manuscript | 19/01/2023 | 25/04/2023 |
| Description of results | 17/10/2022 | 25/01/2023 |

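### The assessment timetable is inconsistent: one section adds a full assessment eight weeks after training, the year of follow-up it claims is not planned, and the calendar can close before the last 6-month calls.

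*Protocol*

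**What the plan says.** **Assessment visits.** Protocol, Procedures and Instruments, puts all participants through the evaluations "at baseline, immediately after the intervention, and eight weeks after the intervention", and adds: "Questionnaires to evaluate the fear of falling and degree of social participation will also be administered at the same time points". Later in the same paragraph only two full assessments are given a duration: "The baseline assessment as well as re-evaluation after eight weeks of intervention will last approximately 40 minutes each".

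The Drawing section has one full reassessment: "After the 8-week intervention period, all parameters will be re-evaluated". Table 2 goes straight from the post-intervention phase to a follow-up phase at months 3 and 6, which contains only the FES-I and LIFE-H. Statistical analysis fits mixed models to "the outcomes measured at the 4 time points (basal, immediately after intervention, and at 3 and 6 months"), and the Summary lists the same four points.

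**Length of follow-up.** Procedures and Instruments says the telephone calls "will assess whether the effect of the training has been maintained over a year". That section and the Drawing section both place the calls at 3 and 6 months after the first reassessment.

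**Calendar (day/month/year).** The Execution Schedule has "Screening of participants | 02/04/2021 | 05/10/2021" and "Data Collection | 04/05/2021 | 09/05/2022". Data analysis starts on 12/05/2022.

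**The concern.** Three statements about timing do not agree with the rest of the protocol.

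1. Staff who follow Procedures and Instruments would bring participants back for strength, gait speed, chair-stand and lean-mass tests eight weeks after training ends. Table 2 has no such visit and the model has no such time point. The Primary outcome section speaks only of changes and names no time point, so it does not settle the matter. At stake is whether a second set of primary-outcome measurements is collected without a planned use.
2. The stated purpose of the calls is a maintenance period longer than the planned contacts cover, and it is worded as the effect of training in general when only two questionnaires are repeated.
3. The calendar leaves too little time for the 6-month call of anyone who enters near the end of screening. At stake is the completeness and timing of the month-6 FES-I and LIFE-H.

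**Working it through.** **Visits, side by side**

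| Section | Full assessments | Questionnaire-only contacts |
|---|---|---|
| Procedures and Instruments (schedule sentence) | baseline, end of training, 8 weeks after training | months 3 and 6 |
| Procedures and Instruments (duration sentence) | baseline, after 8 weeks of training | – |
| Drawing | baseline, after 8 weeks of training | months 3 and 6 |
| Table 2 | baseline, post-intervention | months 3 and 6 |
| Statistical analysis; Summary | baseline, post-intervention | months 3 and 6 (four points in all) |

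The schedule sentence names the end of training and eight weeks after it as separate occasions. Read literally, they are weeks 8 and 16 from baseline. No other row has the week-16 visit.

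**Length of follow-up**

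- Baseline to last call = 8 weeks + 6 months. For a start on 05/10/2021 this runs to 30/05/2022: 237 days, and 237 / 30.4375 = 7.8 months.
- From the end of training it is 6 months.
- If the intervals are read as successive (3 + 6 = 9 months after the first reassessment), baseline to last call is 329 days, and 329 / 30.4375 = 10.8 months.

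None of these reaches 12 months.

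**Calendar**

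Inputs: last screening day 05/10/2021, close of data collection 09/05/2022 and start of analysis 12/05/2022 (Execution Schedule); 8 weeks of training and a follow-up clock that starts at the first reassessment (Drawing; Procedures and Instruments). Assumption: baseline falls on the day of screening. This favours the plan, since any delay widens the gap.

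- End of training: 05/10/2021 + 56 days = 30/11/2021.
- 3-month call: 28/02/2022, which fits.
- 6-month call: 30/05/2022. 30/05 − 09/05 = 21 days after data collection closes; 30/05 − 12/05 = 18 days after analysis starts.
- Latest start that fits: 09/05/2022 − 6 months = 09/11/2021; − 56 days = 14/09/2021, which is 21 days before the last screening day.

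Sensitivity to how 6 months is counted, for the last-day recruit:

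| Reading | Call due | Against 09/05/2022 |
|---|---|---|
| 24 weeks after reassessment | 17/05/2022 | 8 days late |
| 6 months from a last session on 25/11/2021 | 25/05/2022 | 16 days late |
| 6 calendar months after reassessment | 30/05/2022 | 21 days late |
| 26 weeks after reassessment | 31/05/2022 | 22 days late |
| successive 3 + 6 months | 30/08/2022 | 113 days late |
| 6 months from baseline | 05/04/2022 | fits, 34 days to spare |

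Only a clock started at baseline fits, and the protocol does not start it there.

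**How many participants.** The protocol gives no accrual rate. If enrolment were even over the part of the screening window that overlaps data collection (04/05 to 05/10/2021, 154 days), 21/154 = 14%, about 9 of 66. Over the whole screening window (02/04 to 05/10/2021, 186 days), 21/186 = 11%, about 7 of 66. If enrolment ends by 14/09/2021, the number is zero.

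**The case against.** The extra visit rests on a single phrase. The same paragraph goes on to describe the reassessment as following eight weeks of training, and every other section has one post-training measurement, so a slip is the likeliest explanation. A reader might infer that the primary time point is left open between two visits. The documents do not support that: Table 2, the Drawing section, the Summary and the analysis all point to the end-of-training visit. What stands is that the sentence, as written, instructs staff differently.

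The year-long claim appears once. No objective, outcome or analysis repeats it, and the model stops at month 6. A reader might infer that the trial plans a one-year conclusion, but nothing in the analysis would produce one. The absence of strength, gait and lean-mass measures at months 3 and 6 is openly stated and is not itself a contradiction. What stands is that the sentence promises something the planned contacts cannot show.

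On the calendar, a reader might infer that late recruits lose their 6-month outcome and that this biases the comparison. Neither follows. The protocol sets no window around the call, so a last-day recruit could be called up to 21 days early, or data collection could be extended. A cut-off by date does not depend on the participant's outcome and falls on both randomised arms alike. The dates are also a forecast, and recruitment may finish sooner. What stands is that the stated dates cannot hold an on-time 6-month call for everyone the screening window allows.

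**Conclusion.** The inconsistencies are real and should be corrected; their consequences are limited.

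- **Extra visit.** It touches the primary outcomes, because it would add a second post-training measurement that the stated analysis does not use. It is probably a wording slip, but the documents do not prove which schedule was intended.
- **Follow-up claim.** It is wrong on any reading of the call schedule: 6 months after training, about 7.8 months from baseline, and for two questionnaires only.
- **Calendar.** It is short by 21 days for a participant who starts on the last screening day. This assumes baseline on the day of screening and calendar months counted from the first reassessment. The 7 to 9 of 66 affected rests on even enrolment, which is an assumption; the figure is zero if enrolment ends by 14/09/2021. The loss would be some precision, or some early timing, in the month-6 FES-I and LIFE-H. The 3-month call and the end-of-training primary outcomes are unaffected.

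No sample-size, power or alpha figure depends on any of this.

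**What to change.** 1. Reconcile the schedule sentence in Procedures and Instruments with Table 2 and Statistical analysis. Either delete the assessment eight weeks after training, or carry it through Table 2 and the model. If Table 2 stands, state that the end-of-intervention visit is the one used for the primary outcomes.
2. Replace the reference to a year with a period of 6 months after training, for fear of falling and social participation.
3. Extend data collection to at least 30/05/2022 and start analysis after it, or keep the 09/05/2022 close and end enrolment by 14/09/2021.

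Items 1 and 2 are wording only if Table 2 stands; keeping the extra assessment would mean one more visit per participant. Item 3 costs about three weeks, either at the end of data collection or off the screening window.

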**Inclusion criteria:**

The study will include a convenience sample of seniors of both sexes above 60 years of age, with a cognitive level that is adequate to understand the evaluations and interventions of the study. The subjects will be recruited from the geriatric outpatient clinic of the University Hospital of the Federal University of Juiz de Fora (HUCAS/UFJF), and will be invited through posters that will be put up to publicize the study, and/or by invitation of the researcher in the waiting room during their visits to the outpatient clinic.

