**Exclusion criteria:**

Elderly people with cognitive changes detected on the basis of cutoff score < four on the Six Item Screener (ANNEX I) proposed by Callahan et al. (2001), presence of an inflammatory disease in the acute phase, acute cardiovascular and metabolic diseases, neoplasia active in the previous five years, use of anti-inflammatory drugs, presence of neurological sequelae, fractures or surgical osteosynthesis in the last six months, and severe visual and hearing difficulties will be the criteria for exclusion. These diseases or comorbidities will be researched from the patient's medical records at the geriatric outpatient clinic, where they will be followed up and investigated by a screening instrument.

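### The Six-Item Screener score is described as a count of errors, but the exclusion cutoff of below four fits only a count of correct answers

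*Protocol*

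**What the plan says.** The Six-Item Screener is described in the protocol under Procedures and Instruments. It has six items: the text says that it "consists of parameters to check the temporal orientation (three items) and late memory (three items"). The scoring is given as: "Its score ranging between zero and six, is easily marked by a simple sum of errors". The paragraph ends with the rule: "patients who score less than four will be considered as having cognitive impairment and will be excluded from the study".

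The Exclusion criteria restate the rule as: "Elderly people with cognitive changes detected on the basis of cutoff score < four on the Six Item Screener (ANNEX I"). They do not say what the score counts.

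Two other places show the intended population. The Inclusion criteria ask for older people "with a cognitive level that is adequate to understand the evaluations and interventions of the study", and the Summary describes participants as free of cognitive impairment. Nowhere does the protocol say that the score is a number of correct answers.

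**The concern.** A score that adds up errors rises as performance worsens. A rule that calls people impaired when they score below four assumes the opposite. Someone who scores the screener by the protocol's only description of it, and then applies the cutoff, turns away a person who makes no errors and passes a person who fails every item.

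This cutoff is the only numeric rule that puts the cognitive requirement into practice; the inclusion criterion on understanding the study has no score or method attached. The trial relies on that understanding. In the electrostimulation arm participants keep their perceived effort between 5 and 7 on a 0 to 10 scale, and current intensity follows individual tolerance. In the resistance arm they are asked about effort throughout. All of them answer 59 LIFE-H items and 16 FES-I items (59 + 16 = 75), with the 3- and 6-month rounds by telephone. If the screener were applied the wrong way round, the enrolled population would differ from the intended one, and no later analysis could repair that.

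**Working it through.** There is no sample size, power or error-rate figure to reproduce here. The check is to apply the stated cutoff to every possible result under each scoring direction.

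Inputs, all from the protocol:
- Items: 3 temporal orientation + 3 late memory = 6, so errors e run from 0 to 6 (Procedures and Instruments).
- Cutoff: exclude if the score is below 4 (Procedures and Instruments; Exclusion criteria).
- Stated scoring: score = e (Procedures and Instruments).
- Alternative scoring: score = correct answers = 6 − e.

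Rules:
- Errors reading: exclude if e < 4, that is e = 0, 1, 2 or 3.
- Correct-answers reading: exclude if 6 − e < 4, that is e > 2, so e = 3, 4, 5 or 6.

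| Errors | Correct | Score = errors | Score = correct answers | Same decision? |
|---|---|---|---|---|
| 0 | 6 | excluded | passes | no |
| 1 | 5 | excluded | passes | no |
| 2 | 4 | excluded | passes | no |
| 3 | 3 | excluded | excluded | yes |
| 4 | 2 | passes | excluded | no |
| 5 | 1 | passes | excluded | no |
| 6 | 0 | passes | excluded | no |

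The decisions differ for e = 0, 1, 2 and for e = 4, 5, 6, which is 3 + 3 = 6 of 7 results. They agree only at 3 errors.

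The next question is which reading fits the protocol's own purpose. The rule in Procedures and Instruments labels those below four as impaired. The Exclusion criteria attach cognitive changes to a score below four. The Inclusion criteria and the Summary want people without impairment. All of these fit the correct-answers reading, under which 4 to 6 correct passes and 0 to 3 correct is excluded. Only the descriptive phrase about errors points the other way.

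The annexed form might settle the direction, but it is not available, and its label is inconsistent. Procedures and Instruments place the screener in Annex II and use Annex 1 for the general Screening Instrument, while the Exclusion criteria cite the screener as "cutoff score < four on the Six Item Screener (ANNEX I").

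**The case against.** The best defence is that the rule itself is clear. Both statements of the cutoff tie a low score to impairment, and the only outlier is a descriptive phrase about the instrument, quite possibly a translation slip. Screening would be scored from an annexed form that may be right. The separate inclusion criterion on adequate understanding would still stand in the way of someone who failed most items, and turning away perfect performers would probably be noticed early. Screening also precedes randomisation and applies to both arms alike, so the comparison between arms is not biased by this.

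Most of that stands, and it limits the point. A reader might infer that eligibility is completely inverted; it is not, because 3 errors is excluded on both readings. A reader might also infer that the trial will enrol impaired people and turn away intact ones. The document does not support that either: passing the screener is not sufficient for entry, the intent is evident, and the form cannot be seen.

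The defence does not remove the contradiction. The phrase about errors is the only statement of how the score is formed, and it sits directly before the cutoff that uses it. A reader can see that a low score is meant to be bad, but must override the written scoring to apply the rule as intended.

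**Conclusion.** The point holds as an internal contradiction in an eligibility rule. With the score counted as errors, the cutoff of below four reverses the screening decision for 6 of 7 possible results relative to the correct-answers reading, and contradicts the aim set out in the Summary, Inclusion criteria and Exclusion criteria. The 6 of 7 counts possible scores, not people: the share of candidates affected depends on how scores are distributed among those screened, which the protocol does not give.

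Harm to enrolment is possible but not demonstrated. The conclusion that the phrase, and not the cutoff, is the slip rests on the protocol's stated aim and on two concordant statements of the rule. It needs no outside source.

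**What to change.** - In Procedures and Instruments, replace the phrase describing the score as a sum of errors with the number of correct answers, 0 to 6. This is the reading under which the existing cutoff agrees with the protocol's aim, so the number four does not change.
- In the Exclusion criteria, state the same direction: fewer than four correct answers.
- Check that the annexed form scores in that direction, and give the screener one annex number in both sections.
- If anyone has already been screened, confirm which direction was used.

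The cost is two short wording edits, one cross-reference correction and a look at the form. Sample size, outcomes and analysis are untouched.
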